#### QRISK3

- Gives the likelihood of a patient without established cardiovascular disease developing it within the next 10 years
- **Calculate for all patients** at <https://www.qrisk.org/three/index.php> using admission HDL/total cholesterol level
  - If total cholesterol  $> 7.5$  mmol/l or non-HDL cholesterol  $> 5.9$  mmol/l QRISK3 should not be used; repeat fasting lipid profile and assess for familial hypercholesterolaemia using FATS7 strategy (see reference)

#### Treatment with statins

*Switch any existing statin prescriptions to those recommended below. Before starting, check ALT is not  $> 3 \times$  upper limit of normal and there is no unexplained muscle pain (see FATS7)*

- ***Patients with known CAD should be taking atorvastatin 80mg OD***
- ***Patients without the above, but who have QRISK3  $\geq 10\%$  should be taking atorvastatin 20mg OD***

- Additionally, patients over 40 with type 1 diabetes, or with CKD at any age (defined as albuminuria or eGFR <60ml/min/1.73m^2), should be offered atorvastatin 20mg OD regardless of QRISK3 score
- *Patients with QRISK3 < 10% but with CT calcium score ≥ 1 should be taking atorvastatin 20mg OD*

### Treatment with aspirin

- *All patients with known CAD should be taking aspirin 75mg OD*
- *All patients with CT calcium score ≥ 100 should be taking aspirin 75mg OD*
  - If intolerant of aspirin prescribe clopidogrel 75mg OD
- Co-prescribe lansoprazole 15mg OD if age ≥ 75 and/or history of GI bleed/peptic ulcer disease/severe gastro-oesophageal reflux disease

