| CT coronary artery calcification score and CT chest | X γ |         |                                                                                                                                                                                                                                                                                                               |
| 24 hour BP monitor ☉                     | X              |         |                                                                                                                                                                                                                                                                                                               |

Echocardiography will be performed by a trained clinician or British Society of Echocardiography (BSE) trained physiologist with oversight by an independent consultant imaging cardiologist. If image quality is insufficient for accurate assessment of ventricular function, contrast echocardiography using SonoVue contrast agent will be performed during inpatient admission.

CT Coronary artery calcification score will be performed according to standard protocol by a trained consultant Cardiologist. Reporting will be performed blinded to the presence of known CVD and knowledge of severity of COPD and ECOPD. Assessment of whether CVD is treated adequately will be made with reference to (inter)national guidance. CT chest will be performed without intravenous contrast according to standard local protocol; emphysema severity and airway wall thickening quantified using commercially available software. Slots for CT scanning for of the study are available at the start of the morning list so it is anticipated that all patients will be able to have a CT scan before being discharged. If this is not possible patients can have their CT scan on an urgent outpatient basis, within 7 days of discharge. This will avoid discharge being delayed for study investigations. If patients have had a CT coronary artery calcium score calculated within 6 months prior to recruitment, this test will not be repeated as the score is unlikely to have changed significantly in this time.

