### SCATECOPD management summary: lipids and coronary artery disease

#### Rationale and definitions

- Statins are likely to be required in a high percentage of patients in the SCATECOPD study, either because of known coronary artery disease (CAD) or because of high risk of future CAD-related events
- Known CAD is defined as previous myocardial infarction (MI) or coronary revascularisation
- CT calcium score ranges between 0 and 1000+
  - Scores  $\geq 100$  are regarded as moderate to severe and have been demonstrated to correlate with significant coronary artery stenosis and a risk benefit-ratio favouring primary prevention with aspirin

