#### **Anticoagulation:**

- Calculate CHA2DS2-VASc and HAS-BLED scores and review echo report for evidence of mitral stenosis
- Start anticoagulation if CHA2DS2-VASc score  $\geq 1$  in men or  $\geq 2$  in women, unless bleeding risk considered excessive, e.g. recent bleeding event, HASBLED score  $\geq 3$  with risk felt to outweigh benefit
  - If moderate-severe mitral stenosis start warfarin therapy according to local guideline
  - Otherwise start apixaban 5mg BD
    - Reduce to 2.5mg BD if creatine clearance 15-29 ml/min
    - Also reduce to 2.5mg BD if creatine  $> 133\mu\text{mol/L}$  is associated with weight  $< 61\text{kg}$  or age  $> 80$  years
  - If eGFR  $< 15$ , do not use apixaban; offer warfarin
- Stop any antiplatelet drugs (aspirin or clopidogrel) being given for primary prevention of cardiovascular disease, or for secondary prevention after a vascular event (such as MI, stroke) more than 12 months ago
  - If on antiplatelets for a vascular event within 12 months, consult with the specialist who started the antiplatelets before stopping

Quick reference CHA2DS2-VASc and HAS-BLED scores (see references for full details)

| CHA 2 DS 2 -VASc risk | Score |
|---------------------------------------------|-------|
| CHF or LVEF $\leq 40\%$                     | 1     |
| Hypertension                                | 1     |
| Age $\geq 75$                               | 2     |
| Diabetes                                    | 1     |
| Stroke/TIA/VTE                              | 2     |
| Vascular disease                            | 1     |
| Age 65-74                                   | 1     |
| Sex =Female                                 | 1     |

| HASBLED risk                  | Score  |
|-------------------------------|--------|
| Hypertension                  | 1      |
| Abnormal liver/renal function | 1 or 2 |
| Stroke                        | 1      |
| Bleeding history              | 1      |
| Labile INR                    | 1      |
| Elderly (Age $> 65$ )         | 1      |
| Drugs causing                 | 1      |

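### Aspirin in anticoagulated AF patients: the coronary summary says take it, the AF summary says stop it, and neither refers to the other

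*Protocol*

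**What the plan says.** The lipids and coronary artery disease summary in Section S2 has two unconditional rules under Treatment with aspirin: "All patients with known CAD should be taking aspirin 75mg OD" and "All patients with CT calcium score ≥ 100 should be taking aspirin 75mg OD". Clopidogrel is the substitute for patients intolerant of aspirin. Under Rationale and definitions, known CAD means a past MI or coronary revascularisation, with no time limit. Aspirin at a calcium score of 100 or more is justified there by "a risk benefit-ratio favouring primary prevention with aspirin".

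The atrial fibrillation summary, under Anticoagulation, says "Stop any antiplatelet drugs (aspirin or clopidogrel) being given for primary prevention of cardiovascular disease". It extends the same instruction to patients whose last vascular event lies over a year back. For more recent events it adds: "If on antiplatelets for a vascular event within 12 months, consult with the specialist who started the antiplatelets before stopping".

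On the timing of the CT, the Schedule of Activities section expects the scan before discharge but allows a fallback: "If this is not possible patients can have their CT scan on an urgent outpatient basis, within 7 days of discharge". The same section sets the standard for judging treatment: "Assessment of whether CVD is treated adequately will be made with reference to (inter)national guidance". The Cardiovascular treatments section leaves optimisation to the GP and makes the treatment protocols available online to primary care.

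**The concern.** The two summaries give opposite instructions for one identifiable group of patients. The coronary rule applies to all patients who meet its criteria. The AF rule withdraws the same drugs from the same people once they are anticoagulated. Neither summary says which prevails.

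The stake is bleeding. Read literally, the coronary summary adds aspirin or clopidogrel to an anticoagulant in patients for whom the trial's own AF summary wants the antiplatelet stopped. The Methods section says that standardised treatment protocols will be followed, so these summaries are part of the intervention. Under Importance to patients and the NHS, the sponsor also hopes to carry the assessment into a definitive trial and wider use, so an uncorrected conflict would travel with it.

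**Working it through.** The Protocol gives no figure of its own on this point, so the main check is textual.

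**The rules side by side, for a patient anticoagulated for AF**

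| Patient | Coronary summary | AF summary | Result |
|---|---|---|---|
| (a) Calcium score ≥ 100, no vascular event | Take aspirin (labelled primary prevention) | Stop (primary prevention) | Conflict |
| (b) Known CAD, last event > 12 months ago | Take aspirin | Stop | Conflict |
| (c) Known CAD, event within 12 months | Take aspirin | Consult the specialist before stopping | No direct conflict |

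AF that is not anticoagulated is outside the conflict, because the stop rule sits under the Anticoagulation heading.

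**Is there a cross-reference?** The coronary summary does not mention AF or anticoagulants. The AF summary does not mention the coronary summary or the calcium score. The heart failure summary tells readers to address AF and CAD using the relevant recommendations, but sets no order of precedence. The coronary summary does consider bleeding, adding lansoprazole at age ≥ 75 or with certain upper gastrointestinal histories, but concurrent anticoagulation is not among its triggers.

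**Order of events.** The AF rule acts on drugs already being given. If the CT is done after discharge, the calcium score can arrive once anticoagulation has begun. The coronary rule then triggers aspirin, and nothing in the AF summary says not to start it. This route matters only for case (a), since known CAD is established from history.

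**Can both rules apply to the same patient?** The AF summary anticoagulates at a CHA₂DS₂-VASc score of at least 1 in men and 2 in women, unless bleeding risk is judged excessive. Counting a previous MI as vascular disease (the quick-reference table does not define the term), and with no other risk factor:

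- man: 1, threshold 1, met
- woman: 1 + 1 (sex) = 2, threshold 2, met

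So a previous MI alone is enough for the AF summary to call for anticoagulation. This says nothing about case (a), where the score depends on other factors.

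**Rough size**

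- Intervention arm: 60 (Lay summary).
- AF prevalence: 17% to 35% (Scientific Rationale). 0.17 × 60 = 10.2; 0.35 × 60 = 21.
- Share of AF patients with a calcium score ≥ 100 or known CAD: assumed 30% to 70%; the documents give no figure.
- Low end: 0.30 × 10.2 = 3.1. High end: 0.70 × 21 = 14.7.

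That is about 3 to 15 of 60. The range is not reduced for AF left without anticoagulation or for events within 12 months, so it errs high for a given overlap.

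**Secondary mismatch.** Take a patient with AF, LVEF below 45%, resting heart rate above 110 and no current bisoprolol. The heart failure summary (Acting on echo reports) starts bisoprolol at 1.25 mg, provided there is no second- or third-degree AV block. The AF summary (Rate control) starts it at 2.5 mg. Neither says which applies.

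**The case against.** The best counter-argument is that the AF rule is the specific one and the coronary rule the general one. Its wording covers any antiplatelet given for primary prevention, which is how the coronary summary describes calcium-score aspirin. A clinician with both pages open would reasonably conclude that aspirin should stop. All the summaries sit in one appendix, and the heart failure summary sends readers across them. The Cardiovascular treatments section also keeps clinicians tied to local or (inter)national guidelines, which should protect some patients. The post-discharge CT is a fallback, since the Protocol expects scans before discharge.

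Much of this is fair, and it limits how often harm would follow. It does not remove the contradiction. The precedence of the AF rule is a plausible inference that is written nowhere, while the coronary rule says all patients. A reader who opens only the coronary summary sees no warning.

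Three narrower limits stand. The restriction of the stop rule to anticoagulated patients is the natural reading of its heading but is not spelled out. An elective revascularisation without MI is not clearly a vascular event. The patient count rests on an assumed overlap, and it counts people to whom both rules could apply, not people who would receive both drugs. The bisoprolol point is minor: patients with LVEF below 45% are referred to the heart failure service, which supervises the dose.

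**Conclusion.** The concern holds. For patients anticoagulated for AF in cases (a) and (b), the Protocol gives contradictory antiplatelet instructions, and the coronary summary followed as written gives the less safe one. This is a stated rule that produces a wrong result, not a detail left for later. It should be corrected.

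The number affected is perhaps 3 to 15 of the 60 intervention patients, given the cited AF prevalence and an assumed 30–70% overlap. The contradiction itself does not depend on that estimate. The primary endpoint, sample size and error rates are untouched, and undertreatment is still judged against (inter)national guidance.

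**What to change.** 1. In the coronary summary, under Treatment with aspirin, add an exception covering aspirin and the clopidogrel substitute: *except in patients anticoagulated for AF, where the AF summary's antiplatelet rule applies (stop, unless a vascular event occurred within 12 months, in which case consult the specialist)*.
2. In the AF summary, under Anticoagulation, add: *do not start aspirin or clopidogrel under the coronary summary in these patients, including when the calcium score is reported after anticoagulation has begun*.
3. As a secondary change, add one line to the heart failure and AF summaries, confirmed by the cardiology leads, stating which bisoprolol starting dose applies in AF with LVEF below 45% (for example, that the heart failure schedule prevails).

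Keep (inter)national guidance as the standard for undertreatment. The cost is two cross-reference lines and one dosing line, with no new data, visits or analysis.

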### Follow up and referral

- Patients prescribed statins should have lipid profile repeated at their GP practice at 3-4 months, as well as LFTs
  - If non-HDL cholesterol has not fallen by > 40%, double statin dose up to maximum of 80mg atorvastatin
  - If ALT has risen to > 3x upper limit of normal statin should be stopped
- Patients should be advised to report any new muscle pains to their GP for consideration of the need for treatment cessation, dose reduction and/or measurement of creatine kinase levels
- If non-fasting triglycerides > 4.5 mmol/l a fasting sample should be taken and secondary causes excluded (e.g. uncontrolled diabetes mellitus, hypothyroidism). If fasting level > 10 mmol/l consider lipid clinic referral (see FATS7 for further advice)

### SCATECOPD management summary: atrial fibrillation

#### Definition

Atrial fibrillation (AF) shown on ECG while in hospital or total AF burden > 5 mins on 24h ambulatory ECG monitor

### Treatment goals

1. Assessment of stroke/bleeding risk and introduction of anticoagulation if appropriate
2. Control of heart rate to  $\leq 110$  bpm at rest
  - Use mean of multiple heart rate measurements if inpatient, otherwise single clinic measurement

### Pharmacological therapy

- Send TFTs and if hyperthyroid address this first by obtaining urgent endocrinology advice on need for beta blockade e.g. with atenolol

#### **Anticoagulation:**

- Calculate CHA2DS2-VASc and HAS-BLED scores and review echo report for evidence of mitral stenosis
- Start anticoagulation if CHA2DS2-VASc score  $\geq 1$  in men or  $\geq 2$  in women, unless bleeding risk considered excessive, e.g. recent bleeding event, HASBLED score  $\geq 3$  with risk felt to outweigh benefit
  - If moderate-severe mitral stenosis start warfarin therapy according to local guideline
  - Otherwise start apixaban 5mg BD
    - Reduce to 2.5mg BD if creatine clearance 15-29 ml/min
    - Also reduce to 2.5mg BD if creatine  $> 133\mu\text{mol/L}$  is associated with weight  $< 61\text{kg}$  or age  $> 80$  years
  - If eGFR  $< 15$ , do not use apixaban; offer warfarin
- Stop any antiplatelet drugs (aspirin or clopidogrel) being given for primary prevention of cardiovascular disease, or for secondary prevention after a vascular event (such as MI, stroke) more than 12 months ago
  - If on antiplatelets for a vascular event within 12 months, consult with the specialist who started the antiplatelets before stopping

Quick reference CHA2DS2-VASc and HAS-BLED scores (see references for full details)

| CHA 2 DS 2 -VASc risk | Score |
|---------------------------------------------|-------|
| CHF or LVEF $\leq 40\%$                     | 1     |
| Hypertension                                | 1     |
| Age $\geq 75$                               | 2     |
| Diabetes                                    | 1     |
| Stroke/TIA/VTE                              | 2     |
| Vascular disease                            | 1     |
| Age 65-74                                   | 1     |
| Sex =Female                                 | 1     |

| HASBLED risk                  | Score  |
|-------------------------------|--------|
| Hypertension                  | 1      |
| Abnormal liver/renal function | 1 or 2 |
| Stroke                        | 1      |
| Bleeding history              | 1      |
| Labile INR                    | 1      |
| Elderly (Age $> 65$ )         | 1      |
| Drugs causing                 | 1      |

#### **Rate control:**

- Start bisoprolol 2.5mg OD if HR  $> 110$  bpm at rest
- If already on bisoprolol, increase dose by 2.5mg up to maximum 10mg OD
  - Do not increase bisoprolol if systolic BP  $< 90$  mmHg
- If bisoprolol dose maximised, start digoxin (having corrected any hypokalaemia)
  - If in hospital, load with 0.75 to 1.5mg orally in divided doses over 24h, then give maintenance dose 125 micrograms OD (62.5 micrograms OD if eGFR  $< 15$ )
  - Out of hospital, slow loading with maintenance dose is acceptable

### Follow up/specialist referral

- Refer patients started on warfarin to their local anticoagulation clinic for INR monitoring
- Review at GP should take place in 2 weeks following a change in rate control medication, for assessment of pulse rate and side effects and further dose titration if necessary

- patients on digoxin may have dose increased if rate control poor, alternatively if toxicity suspected (nausea, fatigue, blurred vision) a trough level should be checked and dose reduced if level > 1ng/ml
- Cardiology referral should be made for patients if heart rate >110 bpm on maximal digoxin and bisoprolol dose

## Diagnosis and treatment target

### **Blood pressure (BP) ≥ 140/90 mmHg on two occasions in final 24 hours of admission**

- Only one of systolic or diastolic BP needs to exceed the threshold
- Final 24 hours of admission chosen due to lack of evidence for diagnosing hypertension during acute illness

**Treatment target is below 140/90 mmHg in patients under 80 and below 150/90 in patients over 80**

Management of BP during inpatient admission - Consider drug interactions and contraindications and use lowest risk agent

### **Do not start treatment in hospital if BP less than 180/120 mmHg**

- Instead refer patients with BP ≥ 140/90 mmHg on two occasions in final 24 hours of admission for ambulatory blood pressure monitoring (ABPM)

### **Start treatment in hospital if BP ≥ 180/120 mmHg on two occasions**

- These patients should also have urine tested for dipstick haematuria and albumin:creatinine ratio.
  - If they have symptoms/signs attributable to hypertensive end-organ damage, such as headache, they will need specialist inpatient management of their hypertension, usually by an endocrinologist
    - If <55, or co-morbid type II diabetes or heart failure at any age, start ramipril 1.25mg OD
    - If >55, or of black African or African-Caribbean family origin, start amlodipine 5mg OD
- On discharge, ask GP for review within 2 weeks for BP measurement and dose titration**

### **Uptitrate medications in patients already on antihypertensives with BP ≥ 140/90 mmHg on two occasions**

- If on ACE-i, double dose, up to maximum advised in BNF
- If already on maximal ACE-i dose, double CCB dose up to maximum advised in BNF
- If already on maximal ACE-i and CCB doses, add indapamide 2.5mg OD

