Those randomised to the structured cardiovascular assessment will also undergo:

|                                                     | Baseline       | 90 days | β – troponin T, NT pro-BNP, fibrinogen, cholesterol profile (admission only), HbA1c (admission only); γ - performed at any point during index hospital admission (or within 7 days of admission); ☉ - performed in patients hypertensive during initial hospital stay, without a prior hypertension diagnosis |
|-----------------------------------------------------|----------------|---------|---------------------------------------------------------------------------------------------------------------------------------------------------------------------------------------------------------------------------------------------------------------------------------------------------------------|
| ECG                                                 | X              | X       |                                                                                                                                                                                                                                                                                                               |
| Echocardiogram                                      | X              | X       |                                                                                                                                                                                                                                                                                                               |
| Laboratory investigations β              | X              | X       |                                                                                                                                                                                                                                                                                                               |
| 24 hour cardiac monitor                             | X              |         |                                                                                                                                                                                                                                                                                                               |

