## Cardiovascular treatments

For any cardiovascular disease identified, treatment will be initiated by the usual care team in keeping with current local (Northumbria Healthcare NHS Foundation Trust) or (inter)national guidelines. No novel treatment regimens are being examined in this study. Communication with the patient's primary care team will be clear and optimisation of treatment will be performed by the GP, in keeping with (inter)national guidance. In order to facilitate optimum communication between secondary care, primary care and the patient, management summaries (summarising the relevant current guidance reflecting best practice) will be written by the supervisory team with the input of local General Practitioners and an expert patient representative. Treatments given to patients will be recorded at follow up visits as part of the assessment of the rate of undertreated cardiovascular disease (a secondary study outcome). Treatment protocols will be accessible online in primary care and published on the trust website. Treatment of patients in usual care arm will be at the discretion of the treating clinicians.

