**On discharge, ask GP for review in 2-8 weeks for BP measurement and dose titration**

### Acting on ABPM

**≥ 14 measurements taken during usual waking hours should be used**

**Hypertension is confirmed if daytime average is ≥ 135/85 mmHg**

- If not on any antihypertensives, start ramipril or amlodipine as described for inpatients above

- If already on antihypertensives, uptitrate medications as described for inpatients above

*Ask GP for review in 2-8 weeks for BP measurement dose titration*

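### The hypertension summary's uptitration trigger has no age condition, so on the natural reading it escalates treated patients over 80 whose systolic pressure of 140-149 mmHg already meets the summary's own target

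*Protocol*

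**What the plan says.** All of the text at issue is in the protocol, Section S2, in the management summary for hypertension.

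- **Target.** "Treatment target is below 140/90 mmHg in patients under 80 and below 150/90 in patients over 80".
- **Rule for patients already treated.** "Uptitrate medications in patients already on antihypertensives with BP ≥ 140/90 mmHg on two occasions". The first step under it is "If on ACE-i, double dose, up to maximum advised in BNF". The next steps are to double the calcium-channel blocker and then to add indapamide. None of the steps mentions age.
- **How 140/90 is to be read.** Under the diagnostic rule, which uses the same figure, the summary says: "Only one of systolic or diastolic BP needs to exceed the threshold". The uptitration rule does not say whether one component is enough.

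The Methods section says that cardiovascular disease identified in the intervention group will be treated by standardised protocols. The Cardiovascular treatments section says that the usual care team starts treatment in line with guidelines, that "optimisation of treatment will be performed by the GP, in keeping with (inter)national guidance", and that the management summaries condense current best practice for that purpose.

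**The concern.** For someone already on antihypertensive drugs, the escalation trigger is the means by which the target is pursued, so the two should use the same limits. Under 80 they do. Over 80 the target is relaxed to 150 mmHg systolic but the trigger stays at 140 mmHg, and nothing elsewhere in the summary says which figure prevails.

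Two things are at stake, both modest. One is consistency: two clinicians using the same summary could reasonably treat the same patient differently, one leaving the drugs alone because the target is met and the other increasing them because the trigger is met. The other is safety: some of the oldest patients could have doses raised at pressures that the summary itself counts as controlled.

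**Working it through.** No sample-size, power or error-rate figure is involved. The check compares two sets of blood-pressure readings. SBP is systolic and DBP diastolic, in mmHg; the trigger readings must occur on two occasions.

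**Inputs (hypertension summary)**

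- Target under 80: below 140/90. Target over 80: below 150/90.
- Uptitration trigger for treated patients: at or above 140/90, any age.
- Either-component convention: stated under diagnosis for 140/90. Applying it to the uptitration rule is an inference.

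**Treated patient under 80, either component**

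- At target: SBP < 140 and DBP < 90.
- Uptitrate: SBP ≥ 140 or DBP ≥ 90.
- The two sets are exact complements. Overlap: none.

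**Treated patient over 80, either component**

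- At target: SBP < 150 and DBP < 90.
- Uptitrate: SBP ≥ 140 or DBP ≥ 90.
- Overlap: 140 ≤ SBP < 150 with DBP < 90. Width: 150 − 140 = 10 mmHg systolic.

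| Reading, patient over 80 | At target? | Uptitrate? | Consistent? |
|---|---|---|---|
| 135/85 | yes | no | yes |
| 145/85 | yes | yes | **no** |
| 145/92 | no (DBP) | yes | yes |
| 155/85 | no (SBP) | yes | yes |

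**Alternative: the trigger needs both components**

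- Uptitrate: SBP ≥ 140 and DBP ≥ 90.
- Over 80, at target requires DBP < 90, so the overlap is empty.
- But a treated patient at 170/85 is above target at every age and would never be uptitrated, because DBP is below 90. This reading makes the rule fail in an obvious way, which is indirect support for the either-component reading.

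**After the correction**

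- Over 80, uptitrate: SBP ≥ 150 or DBP ≥ 90. This is the exact complement of the target, so the overlap is empty. The rule under 80 does not change.

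**Number of patients**

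- The intervention arm is 60 of 120 (Lay summary). Those affected must also be over 80, already on antihypertensives, and inside the band on two occasions. The protocol gives none of these proportions, so no count follows.

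**The case against.** The strongest reply is that the mismatch depends on an inference. The either-component sentence belongs to the diagnostic rule, and if the uptitration rule needs both components the overlap disappears. That is correct, and the point should be stated with this condition. It does not remove the point: the summary gives only one way of reading 140/90, and the other reading leaves isolated systolic hypertension in treated patients without escalation.

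A second reply is that a reader could let the age-specific target, which comes first, govern the general rule that follows. That is a sensible way to use the document, but the document does not say so.

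A third is that the protocol leaves room for judgement and limits harm. Treatment follows guidelines, and the GP optimises it. Doses of the ACE inhibitor and calcium-channel blocker are capped at the formulary maximum. The GP reviews the patient at 2-8 weeks, urea and electrolytes are checked within 2 weeks of a change in ACE inhibitor or diuretic dose, and there are stopping rules for the ACE inhibitor. This stands as a reason to rate the matter low. These checks follow a dose change, however, and do not settle when one is due. The caution about interactions and choosing the lowest-risk agent concerns which drug to use, not the threshold.

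A reader might go further and say that the summary gives two opposing instructions. It does not. The target line states a goal and does not say to withhold treatment below it; only the uptitration rule directs an action. The defect is a trigger set tighter than the target.

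**Conclusion.** The point holds as a minor error in the text as written. On the either-component reading, treated intervention-arm patients over 80 with systolic 140-149 and diastolic below 90 mmHg on two occasions are at the stated target and are still to be escalated. The band is 10 mmHg wide. The number of patients cannot be derived and is probably small. The conclusion rests on that reading of the trigger and on the absence of any reconciling text in the summary or in the Cardiovascular treatments section.

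Three wider readings are not supported.

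- **Ambulatory monitoring.** A reader might infer the same conflict in the ambulatory step, which also has no age condition: "Hypertension is confirmed if daytime average is ≥ 135/85 mmHg", followed by "If already on antihypertensives, uptitrate medications as described for inpatients above". But 135/85 mmHg is there a threshold for confirming the diagnosis, and the summary gives no ambulatory target at any age for it to contradict. The Schedule of Activities also limits this test: it is "performed in patients hypertensive during initial hospital stay, without a prior hypertension diagnosis". For the same reason, no ambulatory value for patients over 80 can be drawn from the documents.
- **The undertreated-disease endpoint.** A reader might infer that this secondary outcome is misclassified. The Schedule of Activities section says that adequacy of treatment is judged against national or international guidance, not against this trigger.
- **The trial's main result.** Nothing here touches the definition of the primary outcome, its analysis or the sample size.

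**What to change.** Reword the uptitration rule so that it follows the summary's own target. For example: in patients already on antihypertensives, uptitrate when systolic or diastolic pressure, on two occasions, is at or above the target for the patient's age (140/90 mmHg under 80; 150/90 mmHg over 80). This also settles that one component is enough. The target line says under 80 and over 80, so the clinical leads should say on which side a patient aged exactly 80 falls.

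If the clinical leads intend 140/90 mmHg at all ages, leave the rule's threshold as it is and change the over-80 target instead.

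The cost is one line in one management summary and replacement of the copy made available online to primary care. No visits, tests or patients are added.
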